## Abstract

**Introduction:**

There remains a high unmet need for disease-modifying therapies that can impact disability progression in secondary progressive multiple sclerosis (SPMS). Following positive results of the phase 2 MS-STAT study, the MS-STAT2 phase 3 trial will evaluate the efficacy and cost-effectiveness of repurposed high-dose simvastatin in slowing the progression of disability in SPMS.

**Methods and analysis:**

MS-STAT2 will be a multicentre, randomised, placebo-controlled, double-blind trial of participants aged between 25 and 65 (inclusive) who have SPMS with an Expanded Disability Status Scale (EDSS) score of 4.0–6.5 (inclusive). Steady progression rather than relapse must be the major cause of increasing disability in the preceding 2 years.

Participants will be allocated to simvastatin or placebo in a 1:1 ratio. The active treatment will be 80 mg daily, after 1 month at 40 mg daily. 31 hospitals across the UK will participate.

The primary outcome is (confirmed) disability progression at 6 monthly intervals, measured as change from EDSS baseline score. Recruitment of 1050 participants will be required to achieve a total of 330 progression events, giving 90% power to demonstrate a 30% relative reduction in disability progression versus placebo. The follow-up period is 36 months, extendable by up to 18 months for patients without confirmed progression.

Clinician-reported measures include Timed 25 Foot Walk; 9 Hole Peg Test; Single Digit Modalities Test; Sloan Low Contrast Visual Acuity; Relapse assessment; modified Rankin Scale and Brief International Cognitive Assessment For Multiple Sclerosis. Patient-reported outcomes include MS-specific walking, fatigue and impact scales. A health economic analysis will occur.

**Ethics and dissemination:**

The protocol was approved by the London-Westminster REC (17/LO/1509). This manuscript is based on protocol version 8.0, 26 February 2024. Trial findings will be disseminated through peer-reviewed publications and conference presentations.

**Trial registration numbers:**

NCT03387670; ISRCTN82598726.

STRENGTHS AND LIMITATIONS OF THIS STUDYThe MS-STAT2 trial will be the first phase 3 randomised controlled trial to assess the effectiveness of repurposed simvastatin compared with placebo in slowing the progression of disability in secondary progressive MS as a potential neuroprotective agent.It will be the largest ever investigator-initiated phase 3 trial in progressive MS.There will be a range of trial sites from neuroscience centres to district general hospitals.It will have a relatively high age range (up to 65 years) to increase inclusivity with significant patient and public involvement.A limitation is those who are required to be on a statin for their general health are ineligible to participate.

## Introduction

 Multiple sclerosis (MS) is the most common acquired disabling neurological disease affecting adults in temperate latitudes. It is a progressive disorder of the brain and spinal cord (central nervous system) and with current figures (2023) recording a prevalence of 135 000 in the UK and 2.9M globally.^1^

Secondary progressive MS (SPMS) is characterised by a range of severe problems affecting walking, balance, manual function, vision, cognition, pain, bladder and bowel function.^2^,^4^ Rates of conversion from relapsing-remitting MS (RRMS) to SPMS vary depending on definitions used, access to disease-modifying therapy (DMT) and the time period observed. Estimates vary on the risk of conversion, but a recent study reported that the median time from RRMS onset to SPMS is around 30 years^5^ while a separate meta-analysis of SPMS prevalence estimated this would affect up to 50 000 individuals in the UK.^6^ SPMS also has significant financial costs for the National Health Service (NHS), patients and their caregivers; in the UK, the estimated mean annual cost per patient from the societal perspective ranges between £22 000 (Expanded Disability Status Scale, EDSS 4–6.5) and £34 000 (EDSS 7–9).^7 8^

Unlike RRMS, where there is an increasing number (over 15) of DMTs, therapeutic options for those with SPMS are very limited.^9 10^ Siponimod is the only commonly used DMT licensed in the UK for SPMS, but its use is restricted to patients with recent activity (patients with recent inflammatory disease activity, characterised by relapses or new/enhancing MRI lesions). There is a clear lack of effective treatments to impact disease progression.^11^

The MS-STAT phase 2 trial randomised 140 people with SPMS to receive high-dose simvastatin (80 mg/day) or placebo for 2 years. It showed that simvastatin was safe, well tolerated and reduced the rate of annualised brain atrophy by 43% over 2 years. This was supported by positive effects on some secondary outcomes, including clinician-reported (EDSS) and patient-reported (Multiple Sclerosis Impact Scale-29 v2, MSIS29v2) measures.^12^

Despite previous experimental data showing that statins possess immunomodulatory effects in MS,^13^,^16^ the MS-STAT trial did not demonstrate any shift towards a more favourable systemic immunological signal,^12^ suggesting that alternative mechanisms prevail. Statins suppress astroglial and vascular activation,^17^,^19^ improve vascular perfusion and function,^20^,^22^ and attenuate oxidative damage which protects the brain from chronic hypoxic stress. This is especially germane considering evidence that dysfunctional/reduced blood flow in MS may predispose the tissue to damage.^23^,^27^ In support of this, patients with later-stage MS exhibit vascular^28^,^30^ and brain parenchymal cell dysfunction.^1931^,^33^ It is also clear that there is an increase in prevalence of vascular disease in MS, which impacts on disease severity.^34 35^

Therefore, while the cholesterol-dependent actions of statin treatment have been implicated in the past, most evidence continues to support a predominant role for cholesterol-independent processes. Indeed, using a modelling approach from the MS-STAT trial, it was predicted that the beneficial effect was independent of the reduction in total systemic cholesterol levels, signifying the involvement of upstream intermediate metabolites.^36^ Interestingly, a recent Mendelian Randomisation study, looking at the risk of developing MS, implicated the Rho GTPase pathways,^37^ felt to be central to earlier mechanistic animal work.^38 39^

## Methods and analysis

### Trial objective

Following the promising results of the MS-STAT phase 2 trial,^12^ the MS-STAT2 trial has been designed to determine whether simvastatin can slow the time to confirmed disability progression (CDP), based on the current regulatory standard of confirmed EDSS progression.^40^ The primary objective is to compare the effect of daily use simvastatin (80 mg) versus placebo on disability progression at 6 monthly intervals in patients with SPMS, based on change in EDSS score compared with baseline.

### Trial design and setting

MS-STAT2 will be a randomised, multicentre, double-blinded, prospective, parallel-group trial design. The intervention will be oral simvastatin 80 mg vs placebo for patients with SPMS. Figure 1 illustrates the participant pathway. Online supplemental table 1 outlines the trial activities to be conducted, including the clinician and patient-reported outcomes that will be collected. The trial will be conducted at 31 UK NHS hospitals, a mix of trial sites from neuroscience centres to district general hospitals. Participating hospitals will be geographically spread between England, Scotland, Wales and Northern Ireland. The trial will commence in May 2018 and conclude in August 2024.

**Figure 1 F1:**
[figure not shown]
Participant timeline. EDSS, Expanded Disability Status Scale.

### Eligibility criteria

Participants will be aged between 25 and 65 years (inclusive) who fulfil the revised McDonald criteria for MS,^41^,^43^ and have SPMS.^44 45^ Steady progression rather than relapse must be the major cause of increasing disability in the preceding 2 years. The inclusion and exclusion criteria are set out in box 1.

Box 1Inclusion and exclusion criteria
**Inclusion criteria**
Patients with a confirmed diagnosis of multiple sclerosis (MS) who have entered the secondary progressive stage. Steady progression rather than relapse must be the major cause of increasing disability in the preceding 2 years. Progression can be evident from either an increase of at least one point if Expanded Disability Status Scale (EDSS) baseline score <6, or an increase of 0.5 point if baseline EDSS score is ≥6, or clinical documentation of increasing disability.EDSS 4.0–6.5 (inclusive).Aged 25–65 years old.Patients must be able and willing to comply with the terms of this protocol.Provide written informed consent.
**Exclusion criteria**
Relapse within 3 months of baseline visit. Patients will be eligible where 3 months from the final day of the relapse, have elapsed by the date of the baseline visit.Patients who have been treated with steroids (intravenous and/or oral) due to MS relapse/progression within 3 months from the final day of relapse to the baseline visit. These patients may undergo a further screening visit once the 3-month window has expired and may be included if no steroid treatment has been administered in the intervening period.(Patients on steroids for another medical condition may be included in the trial provided the steroid prescription is not for MS relapse/progression).Significant organ comorbidity, for example, cardiac failure, renal failure, malignancy.Screening levels of alanine aminotransferase/aspartate aminotransferase or creatine kinase ≥3×upper limit of normal.Current use of a statin; or any use within the last 6 months.Medications that interact unfavourably with simvastatin as outlined in the current summary of product characteristics (Summary of Medicinal Product Characteristics); including but not limited to CYP3A4 inhibitors (eg, itraconazole, ketoconazole, posaconazole, voriconazole, fluconazole, HIV protease inhibitors (eg, nelfinavir), boceprevir, erythromycin, clrithromycin, telithromycin, telaprevir, nefazodone, fibrates (including fenofibrates), nicotinic acid (or products containing niacin), azole antifungal preparations, macrolide antibiotics, protease inhibitors, verapamil, amiodarone, amlodipine, gemfibrozil, ciclosporin, danazol, diltiazem, rifampicin, fusidic acid, elbasvir, grazoprevir, ticagrelor, daptomycin, grapefruit juice or alcohol abuse.Primary progressive MS.Diabetes mellitus type 1.Uncontrolled hypothyroidism.Female participants who are pregnant or breast feeding. Women of childbearing potential who are unwilling or unable to use an acceptable method to avoid pregnancy for the entire study period, and up to 4 weeks after the last dose of study drug.Use of immunosuppressants (eg, azathioprine, methotrexate, ciclosporine) or disease-modifying therapies (avonex, rebif, betaferon, glatiramer) within the previous 6 months.Use of mitoxantrone, natalizumab, alemtuzumab, daclizumab or other monoclonal antibody treatment, if treated within the last 12 months.Use of fingolimod, dimethyl fumarate, teriflunomide, cladribine within the last 12 months.Use of other experimental disease-modifying therapy within the last 6 months.Commencement of fampridine ≤6 months from the day of randomisation.Concurrent participation in another clinical trial of an investigational medicinal product or medical device.Patients with rare hereditary problems of galactose intolerance, the Lapp lactase deficiency or glucose-galactose malabsorption.

### Recruitment and consent

Participating sites will be centres of expertise in MS and trials in MS; have long-term links with the local MS patient population and will have records of patients who may be eligible to participate.

A national-level registration of interest website will be set up to allow patients to register their interest in the trial, and these details will be transferred to the relevant site trial team for further contact.

In prescreening patients (usually by telephone), sites will provide prospective recruits with the trial’s patient information sheet, and then schedule a face-to-face clinic meeting if the patient expresses interest and appears to meet the eligibility criteria.

At a screening visit, participants will be informed of the aims, methods, benefits and potential risks of involvement in the trial and give documented and recorded informed consent prior to any trial-specific procedures being carried out.

Participants are permitted to either be taking newly licensed DMTs at the time of trial commencement (ie, siponimod) or to begin such use as a concomitant medication while in trial.

A lipid profile will be completed at screening only.

### Treatment allocation

Participants will be randomised in a 1:1 ratio between simvastatin or placebo, based on a minimisation algorithm that incorporates the following factors: sex (male/female); age (< or ≥45 years); EDSS baseline score (≤5.5 or ≥6); whether participants are taking newly licensed (2017 onward) DMTs for SPMS; and trial site. An independent and secure online randomisation service (SealedEnvelope.com) will be used by delegated site staff members to directly allocate participants to a treatment arm. Descriptive information (month and year of birth, initials and trial identifier) will be also entered to ensure randomisation allocation matches the intended participant.

### Blinding

All participants, site investigators (including pharmacy) and the trial sponsor team will be blinded to treatment allocation. Only the randomisation service and trial statisticians have access to unblinded treatment allocations during trial recruitment and follow-up.

On randomisation, a five-digit code will be issued to site staff that identifies a blinded bottle of either simvastatin or placebo according to the participant’s allocation. A hard copy of the code will be taken with the prescription to site pharmacy for direct issuance to the participant. Subsequent bottles (‘maintenance kits’) of simvastatin or placebo will be ordered using the same online service and issued to participant on the same basis as at randomisation.

It is not possible to ascertain from the issuance of kit codes which treatment arm a participant, or group of participants, at any site, is on. Patients will be unblinded as to their treatment arm following the final database lock for trial analysis. There will be a procedure in place for emergency unblinding.

## Intervention

### Form

Oral Sandoz simvastatin 40 mg film-coated tablets or matching placebo.

### Dosage

Participants will receive either simvastatin 80 mg (initially 40 mg at randomisation, then escalated after 1 month) or the same quantity of placebo (of the same colour/size), taken once daily at night.

### Duration

Participants will continue on their allocated treatment arm for between 36 and 54 months. Those who have not experienced CDP by the 36-month point will be offered a further period of follow-up, if they are at a site participating in the trial extension period (see the ‘Discussion’ section). Participants in the extension period will remain on their blinded intervention for a further 6–18 months beyond the 36-month time point, dependant on the time remaining before the end of overall trial follow-up. Participants who discontinue treatment will continue to be followed up unless they withdraw consent from participation in the trial.

### Dose modification and stopping

The dose may be varied for patients experiencing hepatic effects, myopathy/rhabdomyolysis or other adverse events at the principal investigator’s discretion. Where elevated alanine aminotransferase (ALT), aspartate aminotransferase (AST) or creatine kinase (CK) levels are sustained at ≥3×upper limit of normal (ULN), it is recommended that the dose is lowered (from 80 mg (active/placebo) to 40 mg (active/placebo)), with rechallenge at the higher dose possible after parameters return to normal. For ALT, AST or CK levels ≥5×ULN, trial medication should be stopped, with rechallenge only permissible where the intervention was clearly determined to be non-causally related (eg, another intercurrent medication or infection, which has now resolved, produced the biochemical abnormalities).

### Outcomes

#### Primary outcome

The primary outcome will evaluate the effect of daily use of simvastatin (80 mg) versus placebo on disability progression at 6-monthly intervals in patients with SPMS, based on change in EDSS score compared with baseline. Progression of disability will be defined as an increase of at least 1 point if the baseline EDSS score <6, or an increase of 0.5 point if EDSS score ≥6. The initial disability progression event is finalised as positive if the disability is sustained and confirmed ≥6 months later. This allows for disability confirmation to take place if a visit is missed. This is termed CDP. The date of progression (if confirmed) will be the initial date of the progression event. EDSS is generally assessed in person, but there will be capacity for this to be collected remotely via the telephone.^46^ Time to first CDP will be compared between the simvastatin and placebo arms over treatment of up to 54 months. EDSS assessment will be performed by a blinded assessor, in line with the current version of the neurostatus scoring guidance (v04/10.2)

#### Secondary outcomes

Clinician-reported secondary outcomes will include Timed 25 Foot Walk (T25FW); 9 Hole Peg Test (9HPT); Single Digit Modalities Test (SDMT); Sloan Low Contrast Visual Acuity (SLCVA); Relapse assessment; modified Rankin Scale (mRS) and Brief International Cognitive Assessment For Multiple Sclerosis comprising SDMT, California Verbal Learning Test-II (CVLT-II) and Brief Visuospatial Memory Test-Revised (BVMT-R).

Patient-reported outcomes will include MSIS-29v2; Multiple Sclerosis Walking Scale-12 v2 (MSWS-12v2); Modified Fatigue Impact Scale - 21 (MFIS-21); Chalder Fatigue Questionnaire (CFQ).

### Health economic outcomes

For the health economic analysis, the EuroQoL EQ-5D 5 level (EQ-5D-5L) and a bespoke resource use measure (RUM), that is, the Client Services Receipt Inventory (CSRI), will be used.

### Trial schedule

Online supplemental table 1 presents the trial schedule of assessments. Following baseline/randomisation, where a full set of clinical assessments and patient-reported questionnaires will be completed, participants will attend the clinic for safety monitoring and dose escalation at 1 month. At 3 months, participants have a telephone check-up (with safety bloods arranged locally), and then will have further assessment visits at 6-monthly intervals from 6 months postrandomisation onward. Where participants are unable to attend 6-monthly follow-ups (such as due to COVID-19-related issues or participant logistics), a telephone-EDSS assessment will be undertaken,^46^ together with remotely collected patient-reported outcomes and locally performed safety bloods.

In terms of clinician-reported outcomes, the EDSS, 9HPT and T25FW will be performed 6 monthly; the SDMT, SLCVA and mRS annually; and CVLT-II and BVMT-R at baseline and the 36-month visits only. For patient-reported outcomes, the EQ-5D-5L and CSRI will be completed 6 monthly; with the CFQ, MFIS-21, MSIS-29v2 and MSWS-12v2 completed annually.

Participants will be evaluated at the 36-month time point visit to determine whether they have experienced EDSS CDP. Those participants yet to have CDP will be asked to consent to continued follow-up into the extension phase, at sites which agree to take part in the extension, as outlined in the ‘Intervention’ section.

At the lead site (University College London Hospitals Trust) only, additional subsidies will be conducted to investigate MRI, biomarker and optical coherence tomography outcomes.

### Power and sample size

In order to have 90% power to demonstrate a 30% relative reduction in disability progression for simvastatin versus placebo, at the conventional 5% significance level, the trial will require a total of 330 progression events. This will be achieved by recruiting 1050 participants with 525 enrolled on each treatment arm. Individual participant trial duration will be a minimum of 36 months (core) and up to a further 18 months (extension) if there is no confirmed progression event by 36 months. This assumes that the placebo progression rate will be 40% by 36 months and 49% by 54 months^47^,^50^ and allows for 20% loss to follow-up by 36 months and 32% by 54 months (among those who are eligible for the extension). This is equivalent to a progression rate of 8% per 6 months among those who have yet to experience progression.

## Analyses

### Statistical analysis

The primary statistical analysis will be based on all participants as randomised, irrespective of subsequent compliance with allocated treatment (intention-to-treat analysis). A secondary per-protocol analysis will be carried out including only participants who were able to comply (see the ‘Compliance’ section) with simvastatin or placebo treatment.

### Primary outcome

The primary analysis will be a comparison of the time to EDSS initial disability progression (if confirmed ≥6 months later) between the simvastatin and placebo arms. HRs and 95% CIs will be calculated using a Cox proportional hazards model and Kaplan-Meier curves produced. The time scale used for survival analysis will be time since randomisation. Participants will be censored if they die, are lost to follow-up, withdraw from the trial or at the final patient visit at which confirmed progression could take place. The model will allow for between-centre variability by stratification by site (baseline hazard allowed to differ by site). In addition, other variables included in the minimisation process will be included as fixed effects. The assumptions underlying the Cox model will be assessed and if there is clear non-proportionality, HRs will be presented separately for the relevant time periods.

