### Analysis plan

A detailed statistical analysis plan has been written and signed off. All statistical tests will use a two-sided p value of 0.05 unless otherwise specified. Statistical analysis will be performed by using Stata v17.0 (StataCorp).

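### The primary censoring rule ties risk time to confirmable visits only for participants who reach the end, so those who leave contribute risk time in which no event can count

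*Protocol article*

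**What the plan says.** Three statements in the protocol article matter here.

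- Outcomes, Primary outcome, on what counts: "The initial disability progression event is finalised as positive if the disability is sustained and confirmed ≥6 months later".
- The same section, on dating: "The date of progression (if confirmed) will be the initial date of the progression event".
- Analyses, Primary outcome, on censoring: "Participants will be censored if they die, are lost to follow-up, withdraw from the trial or at the final patient visit at which confirmed progression" is still possible.

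The Trial schedule section places EDSS visits every 6 months from month 6. The Power and sample size section allows for 20% loss to follow-up by 36 months, about 210 of 1050 participants, and for 32% by 54 months among those eligible for the extension. It gives no split by arm. The Missing data section provides for further sensitivity analyses, not specified, if withdrawal patterns turn out to differ substantially.

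**The concern.** Onset dating combined with later confirmation means that nobody can have a countable event at their own last attended EDSS visit. The censoring sentence recognises this in its final limb. It does not carry the limit over to people who die, are lost or withdraw.

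Take someone who withdraws at month 29. Their last visit is month 24. If they are censored on leaving, they are in the risk set at month 24, although an onset at month 24 would need an EDSS at month 30 or later. Their last visit with a confirmable onset is month 18. Censoring them at the last attended visit, month 24, leaves the same problem. It arises for every leaver, with or without worsening, and even if leaving has nothing to do with disability.

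At each visit the risk set therefore holds some people who cannot have an event, in proportion to that arm's dropout over the next 6 months. Observed progression is diluted. If dilution differs between arms, the arm losing more people looks better on the primary hazard ratio.

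**Working it through.** **Inputs from the article.** 8% progression per 6 months among those yet to progress; 20% loss by 36 months; "the trial will require a total of 330 progression events"; "90% power to demonstrate a 30% relative reduction in disability progression", taken as HR 0.70; "recruiting 1050 participants with 525 enrolled on each treatment arm"; 6-monthly visits; two-sided 5% ("All statistical tests will use a two-sided p value of 0.05 unless otherwise specified").

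**Assumptions.** Loss splits by arm averaging the stated 20%; constant dropout unrelated to disability; no visits missed before leaving.

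**1. The plan's own figure.** Schoenfeld: d = 4(z₀.₉₇₅ + z₀.₉₀)² / (ln 0.70)² = 4(1.960 + 1.282)² / 0.1272 = 330.4. Power at 330 events is 89.97%. The stated 330 is reproduced, so SE(ln HR) = 2/√330 = 0.110 is used below.

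**2. Hazard under each rule.** Let p be the chance of onset at a visit and c the chance of attending the next one. With loss L by month 36, c = (1 − L)^(1/6).

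- Censoring on leaving: everyone event-free at the visit is at risk, but an onset counts only if the next visit is attended. The observed hazard per visit is p·c.
- Censoring everyone at the last confirmable visit: only those who attend the next visit are at risk. The observed hazard is p.

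The hazard ratio under the first rule is ln(1 − p₁c₁) / ln(1 − p₀c₀), with p₀ = 0.08 and p₁ = 1 − 0.92^HR (0.08 if HR = 1; 0.0567 if HR = 0.70).

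**3. Example, 25% (simvastatin) v 15% (placebo).** c₁ = 0.75^(1/6) = 0.9532 and c₀ = 0.85^(1/6) = 0.9733. With HR = 1: ln(1 − 0.07625) / ln(1 − 0.07786) = 0.07932 / 0.08106 = 0.979.

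**4. All splits, censoring on leaving.**

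| Loss by 36 months, simvastatin v placebo | True HR 1.00 reads | True HR 0.70 reads | Null shift, in SE | Two-sided type I error |
|---|---|---|---|---|
| 20% v 20% | 1.000 | 0.700 | 0.00 | 5.0% |
| 22% v 18% | 0.991 | 0.694 | 0.08 | 5.1% |
| 25% v 15% | 0.979 | 0.685 | 0.20 | about 5.5% |
| 30% v 10% | 0.957 | 0.671 | 0.40 | 6.8% |
| 15% v 25% | 1.022 | 0.716 | 0.20 (other way) | about 5.5% |

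In the last row, power at 330 events falls from 90% to about 86%. Under the uniform rule the results are 1.000 and 0.700 in every row.

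**5. Simulation check.** Cox model with Efron ties, 150,000 per arm, continuous withdrawal times, and maximum follow-up spread evenly over 36, 42, 48 and 54 months (an assumption). Censoring on leaving gave null HRs of 0.981 (25% v 15%) and 0.963 (30% v 10%). The uniform rule gave 0.995 to 1.003 at HR 1 and 0.698 to 0.706 at HR 0.70 over the four splits run, which is simulation noise.

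**6. Kaplan-Meier curve at equal loss.** c = 0.80^(1/6) = 0.9635, so the observed hazard is 0.0771. Progression by 36 months reads 1 − (1 − 0.0771)⁶ = 38.2%, against 1 − 0.92⁶ = 39.4%.

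**7. Sensitivity to the final limb.** If it meant simply the last visit of all, the hazard ratios would not change, because no event can count at that visit in either arm.

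**The case against.** The sentence lists reasons for censoring and never prints a date for death, loss or withdrawal. Operational dates are often left to the analysis plan, which the article says is signed off and which is not shown. This stands as a limit on how firmly the point can be put: a reader might infer that the protocol expressly sets the withdrawal date, and it does not. It does not dispose of the point. The article states the rule and attaches the confirmability limit to one limb only, with the others joined by an "or"-type alternative in plain reading. The Compliance section uses the date of withdrawal as its own cut-off. If the limit was meant for everyone, the sentence still needs rewording.

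A reader might also infer that the primary result will be tilted towards simvastatin. The documents do not support that. They give one overall loss rate and no split. Participants who stop treatment stay in follow-up unless they withdraw consent; telephone EDSS can replace a visit; confirmation may come after a missed visit; and the Introduction reports phase 2 treatment as well tolerated. All of this makes a wide imbalance less likely. The 30% v 10% case is three times the loss on active treatment. If placebo loses more, the shift works against simvastatin.

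The Missing data section covers the situation in which the hazard ratio would shift, but only with unspecified analyses triggered by substantial differences. These would not repair the primary estimate.

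**Conclusion.** The point holds in a limited form. On the natural reading, leavers are kept in the risk set at a visit where no onset could count. Progression is slightly understated in both arms, by about 1.2 percentage points at 36 months under the plan's own 8% and 20% figures (39.4% − 38.2%). The hazard ratio moves only if loss differs between arms: about 1% for a 4-point difference, 2% for 10 points and 4% for 20 points, always in favour of the arm losing more. Plausible imbalance puts it at 1 to 2%, well within one standard error.

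These sizes rest on assumed splits and on dropout unrelated to disability. If people tend to leave after a first worsening, the effect could be larger, but the article gives no figure from which to size it.

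**What to change.** State one rule for all in the protocol and the analysis plan: every participant without confirmed progression is censored at the last EDSS visit that was followed by another EDSS at least 6 months later, or at randomisation if there was none, whatever the reason follow-up ended. Judge the 6 months exactly as for confirming an event.

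Report censoring at the date of leaving as a sensitivity analysis. Add a separate one for participants who leave after an unconfirmed worsening, since the uniform rule neither counts that worsening nor corrects for dropout linked to it.

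The cost is a sentence in each document and two sensitivity analyses. No new data are needed and no countable event is lost, because the risk time removed could never contain one. The change should be made before treatment allocation is unblinded for the analysis.
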